#### Secondary outcomes

The effect of the intervention on upper and lower limb strength, sensation, independence, ability to walk, quality of life, perceptions of the ability to perform self-selected goals, and impressions of therapeutic benefit will be estimated using the same statistical model used in the primary analysis. For outcomes measured at both 10 weeks and 6 months, both visits will be included in the model and correlations between repeated measures will be modelled by including a random patient intercept and the effect of the intervention will be estimated at each visit by a fixed term for visit together with its interaction with the intervention.

Similar models will be used to estimate the effect of the intervention on participants’ impressions of therapeutic benefit. However, as baseline values are not collected for this outcome variable, baseline Total Motor Score will be used in the model as a pre-randomisation covariate.

The effect of the intervention on time to discharge will be estimated from a Cox model that includes baseline Total Motor Score and the stratification variables (severity as a fixed effect and site as a random effect). Patients will be censored at 6 months or when they were last known to be in hospital, whichever occurs earlier.

The effect of the intervention on type of SCI (AIS grade—5 levels) will be estimated using an ordinal logistic regression model that includes baseline AIS grade and the stratification variables. The effect of the the intervention will be estimated as the odds ratio corresponding to the odds of shifting to a worse grade category.

No subgroup, adjusted or imputed analyses are planned for any of the secondary outcomes.

If there is more than 20% non-adherence (defined as less than 80 h of additional motor training), methods of causal inference will be used to estimate the effects of intervention in the principal stratum of people who would comply with both assigned and (counterfactual) unassigned interventions [49]. Modern methods of causal mediation analysis will also be used to determine the extent to which the effects of the intervention are mediated by time spent in training [50, 51].

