### Outcome measures

Outcome data will be collected at baseline (prior to randomisation), and then 10 weeks (±2 weeks) and 6 months (±4 weeks) after randomisation by independent blinded assessors. The baseline and 10-week assessments will be conducted face-to-face and the 6-month assessments will be conducted by telephone. For this reason, motor and sensory scores and AIS grades will not be collected at 6 months. The success of assessor blinding will be monitored and reported.

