### Sample size

A sample size of 220 is needed to provide a 90% probability of detecting a significant between-group difference of 6/100 points on the Total Motor Score (/100 points) 10 weeks after randomisation. The decision to use 6/100 points is based on the recommendations of the Committee representing The International Campaign for Cures of Spinal Cord Injury Paralysis (ICCP) [44]. The committee states that 5 to 10 points reflects a “relatively modest treatment effect”. These calculations assume a SD of the change in Total Motor Scores of 13.3 points, a worst-case loss to follow-up in both groups of 10%, and an alpha value of 0.05. The estimated SD is based on comprehensive data from a large trial provided by the ICCP, and takes into account the exclusion of people with complete injuries and no zones of partial preservation, and the delayed recruitment for up to 10 weeks after injury (see Supplementary Fig. 2, pg 2, 2nd column, 3rd row in reference [44]). Allowance has been made for one interim analysis using the O'Brien-Fleming stopping rule.

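### The two-visit model for secondary outcomes, as written, implies equal variance at 10 weeks and 6 months; allowing visit-specific variances would protect the visit-specific confidence intervals at almost no cost

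*Protocol article*

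**What the plan says.** The Secondary outcomes part of the Data analysis section carries the primary model over to the secondary scales and extends it for repeated visits: "For outcomes measured at both 10 weeks and 6 months, both visits will be included in the model". On the within-patient structure it says that "correlations between repeated measures will be modelled by including a random patient intercept". On the estimates it says that "the effect of the intervention will be estimated at each visit by a fixed term for visit together with its interaction with the intervention". Site remains a random effect through the primary model. The section does not mention visit-specific residual variances, an unstructured covariance, robust standard errors or a baseline-by-visit term.

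The Outcome measures section shows how the visits differ. Their timing is "10 weeks (±2 weeks) and 6 months (±4 weeks) after randomisation", and the mode changes: "The baseline and 10-week assessments will be conducted face-to-face and the 6-month assessments will be conducted by telephone".

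By Table 2, nine analyses have both visits: SCIM-III, WISCI-II, the four WHOQOL-BREF domains, EQ-5D-5L, self-selected goals, and impressions of therapeutic benefit. The last has no baseline value, and the article uses baseline Total Motor Score as its covariate. The primary outcome is outside the point, because "motor and sensory scores and AIS grades will not be collected at 6 months".

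**The concern.** A random patient intercept with a single residual variance is a compound-symmetry model: one total variance shared by both visits, and one covariance. That would matter little if only an average effect over visits were wanted. Here an effect and an interval are wanted at each visit, and each interval would borrow half of its variance from the other visit.

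The design gives reasons to doubt that the adjusted variances are equal. The mode changes from face-to-face to telephone, the window doubles from ±2 to ±4 weeks, and baseline lies further from the second visit. At stake is the calibration of 18 visit-specific intervals (nine analyses, two visits each). If the variances differ, one visit's intervals are anti-conservative and the other's give away precision.

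**Working it through.** **Inputs.** The model, the visits, their mode and their windows come from the sections cited above. The trial size is 220 (Sample size section). The article has no figure on this point to reproduce: its only SD, 13.3, is for change in Total Motor Score, which is not collected at 6 months. The adjusted SD ratio r (6 months divided by 10 weeks) is therefore an assumption and is shown as a range.

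**Step 1: what the model implies.** With intercept variance τ² and residual variance σ², each visit has variance τ² + σ² and the covariance is τ². That is two parameters for a 2x2 matrix with three free elements. With complete data the common variance is estimated by the average (s1² + s2²)/2.

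**Step 2: effect on the standard errors.** At visit k the model standard error divided by the true one is √[(s1² + s2²)/2] / sk. Setting s1 = 1 and s2 = r gives √[(1 + r²)/2] at 10 weeks and the same quantity divided by r at 6 months. Coverage of a nominal 95% interval is 2Φ(1.96 × ratio) − 1.

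For r = 1.25: √[(1 + 1.5625)/2] = √1.28125 = 1.132 at 10 weeks, and 1.132/1.25 = 0.906 at 6 months. Coverage is 97.3% and 92.4%.

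| Assumed r | SE ratio, 10 weeks | SE ratio, 6 months | Coverage, 10 weeks | Coverage, 6 months |
|---|---|---|---|---|
| 1.0 | 1.000 | 1.000 | 95.0% | 95.0% |
| 1.1 | 1.051 | 0.956 | 96.1% | 93.9% |
| 1.2 | 1.105 | 0.920 | 97.0% | 92.9% |
| 1.25 | 1.132 | 0.906 | 97.3% | 92.4% |
| 1.5 | 1.275 | 0.850 | 98.8% | 90.4% |

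If the 10-week visit is the more variable one, the two visits swap places.

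**Step 3: simulation.** The compound-symmetry model was fitted by REML to 220 patients with terms for group by visit, baseline and severity. Site was left out, the within-patient correlation was 0.7, and 10% of 6-month values were missing at random and unrelated to outcome. There were 2000 replicates, so coverage near 95% has a Monte Carlo standard error of about half a percentage point (√(0.05 × 0.95/2000) = 0.49%). Coverage at 10 weeks and 6 months was:

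- r = 1.0: 95.1% and 94.6%
- r = 1.1: 95.9% and 94.6%
- r = 1.25: 97.4% and 91.9%
- r = 1.5: 98.4% and 89.8%

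The mean error of the effect estimates was at most 0.007 of the 10-week SD, so they are essentially unbiased in this setting. A correlation of 0.4 at r = 1.25 gave nearly the same coverage (97.6% and 91.9%).

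**Step 4: how such a ratio could arise.** This is an illustration and uses no trial data. Take equal raw SDs of 1 and one baseline slope b, equal to the average of the two baseline correlations c. The adjusted variance at a visit is 1 − 2bc + b².

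- Correlations 0.7 and 0.6, b = 0.65: variances 0.5125 and 0.6425, SD ratio 1.12.
- Correlations 0.8 and 0.65, b = 0.725: variances 0.3656 and 0.5831, SD ratio 1.26.

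With a separate slope at each visit the variances become 1 − c². These are 0.51 and 0.64 in the first case (ratio 1.12), and 0.36 and 0.5775 in the second (ratio 1.27). The inequality comes from baseline predicting the later visit less well, and a baseline-by-visit term alone does not remove it. The covariance structure has to allow for it.

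**The case against.** The strongest reply is that nothing in the article is false. The sentence on the random intercept describes how correlation is handled. It does not say that residual variance is common to both visits, and a random intercept can be combined with visit-specific residual variances. Such detail is often settled in an analysis plan, which is not shown here. A random intercept is also a standard and defensible choice for two follow-up visits.

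The mode argument has limits too. A move to telephone may shift the mean, which the visit term absorbs, without changing the spread. Several of the scales are reported by the participant in either mode, and no direction for the variance difference is established.

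Much of this stands. A reader might infer that the planned intervals are wrong, or that the plan imposes equal variances outright. The article supports neither: it reports no visit-specific SD, and it is silent on residual variance. What remains is narrower. The article does name its within-patient structure, and in the usual form of that structure the variances are equal. The visit-specific estimates that it wants do not need that restriction.

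**Conclusion.** The point holds conditionally and is a low-cost improvement; it does not show an error in the plan. As written and in its usual form, the model assumes equal adjusted variance at the two visits. If that is true, nothing is lost. If the SD ratio is up to about 1.1, the effect is negligible. At an assumed 1.25, standard errors are about 13% too large at the less variable visit and 9% too small at the other. Unequal variances are plausible from the change of mode, the wider window and the longer time from baseline, but no figure in the article shows them.

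The scope is limited to the secondary outcomes measured twice. The primary outcome and the other outcomes not analysed at two visits are unaffected. The statement that effect estimates remain essentially unbiased rests on the simulation, in which missingness at 6 months was unrelated to outcome.

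**What to change.** In the analysis plan, replace the random patient intercept for the two-visit outcomes with an unstructured 2x2 within-patient covariance (a variance for each visit and one covariance), or state that residual variances may differ by visit. Keep the random site effect and the visit-by-intervention interaction. Add a baseline-by-visit term so that the baseline slope can differ between visits. For impressions of therapeutic benefit, which has no baseline value, use baseline Total Motor Score by visit.

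The cost is one extra covariance parameter and one extra fixed effect per model, with about 198 participants (220 less the 10% loss that the article allows for) and no new data. Most of the protection for the intervals comes from the covariance change. If the variances turn out equal, almost no precision is lost. If an existing analysis plan already allows visit-specific variances, only the published description needs to be aligned with it.

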#### Motor training

Participants allocated to the Motor Training Group will receive, in addition to usual care, an extra 12 h of motor training each week for 10 weeks. This will commence within two business days of randomisation. The 12 h per week of motor training can be provided at any time although it is anticipated that most sites will administer the additional motor training over five 2-h sessions on each weekday of the week. Some sites may provide the training in longer sessions on Saturdays and Sundays, or both. The therapy involves active, targeted motor training of neurologically-weak muscles below the level of the injury, and may consist of practice of functional activities using the principles of task-specific training, or isolated muscle contractions directed at improving strength or motor control. For example, a participant with some motor activity in the lower limbs will receive intensive task-specific training focusing on regaining the ability to sit, stand and walk. This could involve task-specific training of sitting, standing, gait training on a treadmill with bodyweight support or the use of robotic gait devices. A participant with some motor activity in the upper limbs and hands will receive intensive training of a range of reaching and grasping tasks. Training will be supplemented, where available and at the therapist’s discretion, with biofeedback, electrical stimulation, mental imagery and somatosensory stimulation. Robotics and computer game-based therapy will be used where available and appropriate provided they encourage active contraction of neurologically-weak muscles. Importantly, treatments will be individualised to the needs of each participant and follow key principles of task-specific training and strength training as outlined in a detailed intervention manual compiled for the trial. All training will address a participant’s specific motor problems. Details of the motor training provided to participants will be recorded with the same forms used to document usual care.

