### Data analysis

#### Primary outcome

The mean between-group difference in Total Motor Scores at 10 weeks will be estimated with a mixed linear regression model in which Total Motor Score at 10 weeks will be regressed on randomised group, baseline severity of injury (a stratification variable), and baseline motor score. Site (a second stratification variable) will be included as a random effect. Baseline scores will be included in the model to increase precision [45]. Severity of injury and study site will be included in the model to prevent the anti-conservative bias in standard errors that would otherwise be produced by stratification on these variables [46]. The effect of the intervention will be estimated as the adjusted mean between-group difference and confidence interval.

The primary analysis will be performed without replacing missing data. It will be expected to provide unbiased estimates of the intervention effect if data are missing at random conditional on non-missing data [47]. In case of non-negligible amounts of missing primary outcome data at 10 weeks (>5%), we will use controlled multiple imputations to assess under what conditions the results change, and how plausible these conditions are, using the approach described by Cro et al. [48].

A subgroup analysis will examine whether the effect of the intervention is moderated by the type of SCI at baseline (AIS A or AIS C/D), and severity of injury (paraplegia or tetraplegia). The subgroup analysis will be conducted on the primary outcome using a model that is the same as the linear regression model used in the primary analysis except that it contains, in addition, a term for the interaction between group and type of SCI.

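### The AIS-grade model adjusts for a three-level baseline grade but not for the baseline Total Motor Score already held for everyone; adding it may raise power at almost no cost

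*Protocol article*

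**What the plan says.** All statements are in the Protocol article, Data analysis, unless noted.

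- **AIS grade (Secondary outcomes).** The model is an "ordinal logistic regression model that includes baseline AIS grade and the stratification variables". The stratification variables are severity (paraplegia or tetraplegia) and site. The outcome has five levels. Table 1 admits only grades A (with some motor function well below the motor level), C and D.
- **Walking (Secondary outcomes).** Ability to walk is in the list of outcomes that ends "impressions of therapeutic benefit will be estimated using the same statistical model used in the primary analysis". In that primary model, "Total Motor Score at 10 weeks will be regressed on randomised group, baseline severity of injury (a stratification variable), and baseline motor score", with site as a random effect.
- **Impressions of benefit (Secondary outcomes).** Here, "as baseline values are not collected for this outcome variable, baseline Total Motor Score will be used in the model as a pre-randomisation covariate".
- **Time to discharge (Secondary outcomes).** This uses a "Cox model that includes baseline Total Motor Score and the stratification variables".
- **Reason for adjustment (Primary outcome).** "Baseline scores will be included in the model to increase precision".
- **Data held (Table 2).** Total Motor Score, AIS grade and WISCI-II are all scheduled at baseline, and randomisation follows the baseline assessment.

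The article also plans no further adjusted analysis of any secondary outcome, so the covariates named are the ones that will be used.

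**The concern.** The article gives precision as its reason for baseline adjustment. For AIS grade, the only baseline measure of neurological status in the model, apart from paraplegia or tetraplegia, is a covariate with three values. Participants with the same grade can differ in strength, and the model treats them alike. A finer score from the same International Standards examination is available for each of them and is not used.

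If that score predicts the 10-week grade within a baseline grade, the planned comparison has less power than the collected data allow. The trial is sized on Total Motor Score only, and no power is stated for AIS grade or walking. Because the covariates are fixed in advance and no further adjusted analysis is foreseen, adding the score after the results are known would be post hoc.

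For walking the question is which baseline enters the model. The article does not say so directly, and the two readings give different models.

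**Working it through.** **The plan's own figures.** No power, variance or correlation is given for AIS grade or walking. The one sizing figure is 220 for Total Motor Score (difference 6, SD 13.3, alpha 0.05, power 90%, loss 10%). Assuming a two-sided test and 1:1 allocation:

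- n per arm = 2 × 13.3² × (1.960 + 1.282)² / 6² = 103.3, so 104; total 208; 208 / 0.9 = 231.1, so 232, against 220 stated.
- 220 × 0.9 = 198 evaluable, 99 per arm, which gives power of 88.8%.

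The stated 220 is therefore not reproduced exactly, but power is close to 90%. This has no bearing on the present point, except that it supplies 198 as the evaluable number.

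**AIS grade, first simulation.** Proportional-odds data, n = 198, 300 trials per row. All of the following are assumptions: baseline mix A/C/D 15/45/40%, true conditional log odds ratio for treatment 0.8, no site effect. Motor score enters as its standardised value within grade and severity. Both models were fitted to the same data sets; significance is |z| > 1.96.

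| Log-odds per SD of motor score | Mean log OR (SE), planned model | Mean log OR (SE), motor score added | Power, planned | Power, added | Gain (points) |
|---|---|---|---|---|---|
| 0 | 0.833 (0.302) | 0.835 (0.304) | 79.7% | 79.7% | 0 |
| 0.5 | 0.779 (0.299) | 0.811 (0.303) | 73.3% | 76.7% | 3.4 |
| 1.0 | 0.741 (0.291) | 0.862 (0.303) | 69.3% | 80.0% | 10.7 |
| 1.5 | 0.599 (0.282) | 0.808 (0.306) | 58.7% | 73.7% | 15.0 |

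The standard error of the log odds ratio does not fall; it rises slightly in every row. Power rises because the planned model estimates an odds ratio averaged over motor score, which lies closer to 1, while the extended model estimates one conditional on it.

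**AIS grade, second simulation.** A different set-up, n = 198, 300 trials per scenario: assumed mix A/C/D 10/35/55%, within-grade motor-score SD 10 to 12, and conversion from C to D generated by a strength threshold.

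| SD of motor gain | Effect (points) | Power, planned | Power, added | Gain (points) |
|---|---|---|---|---|
| 13.3 | 6 | 31% | 36% | 5 |
| 13.3 | 9 | 66% | 71% | 5 |
| 10 | 6 | 44% | 55% | 11 |
| 10 | 9 | 79% | 86% | 7 |

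The Monte Carlo standard error of one power figure is at most √(0.25/300) = 2.9 points. In this second simulation the rejection rate with no effect was 6 to 8% in both models.

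**Walking.** Let r be the partial correlation of baseline motor score with follow-up WISCI-II, given baseline WISCI-II, severity and site. In a linear model at one visit, adding motor score multiplies the standard error by √(1 − r²). A comparison with 80% power moves to Φ(2.802/√(1 − r²) − 1.960).

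| r (assumed) | SE multiplier | 80% power becomes |
|---|---|---|
| 0.1 | 0.995 | 80.4% |
| 0.2 | 0.980 | 81.6% |
| 0.3 | 0.954 | 83.6% |
| 0.4 | 0.917 | 86.4% |
| 0.5 | 0.866 | 89.9% |
| 0.6 | 0.800 | 93.8% |

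**The case against.** The strongest reply is that nothing here is wrong. The plan uses an outcome's own baseline where there is one and Total Motor Score where there is none. It gives that reason for impressions of benefit, and time to discharge has no baseline either. Adjusting for the outcome's own baseline is standard and introduces no bias. All of this stands. A reader might infer from the contrast between models that the plan is inconsistent or overlooked the score for AIS grade; the documents do not support that. A consistent rule can still be inefficient where the own baseline is coarse, and that is all that is claimed.

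The size is also open to challenge. Every gain rests on assumed prognostic strength. The second simulation builds in a link between strength and conversion. At the protocol's own SD and effect it moves power only from 31% to 36%, so that comparison is weak with or without the covariate. This stands too, and is why the range must start at nil.

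On walking, a reader might infer that motor score is left out. Read literally, the primary model contains baseline motor score, so it is in. The remark about outcomes without baseline values suggests that WISCI-II's own baseline takes its place, and this is the likelier reading, but it is nowhere stated. A reader might also infer that baseline WISCI-II sits near its floor, since training includes work "focusing on regaining the ability to sit, stand and walk". That phrase comes from an example of training content, and grade D is eligible; the documents say nothing about the spread of baseline walking scores.

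**Conclusion.** The point holds as a cheap improvement to secondary analyses, not as an error. The AIS model omits a baseline score that is held for everyone and may be prognostic within grade. The cost in power is nil if it is not prognostic, about 3 points if it is weakly so, and roughly 5 to 15 points under moderate to strong prognostic strength. These figures depend on the assumed grade mix, treatment effect and strength of prediction, none of which the article gives.

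Two stronger conclusions should not be drawn. First, confidence intervals for the AIS odds ratio are not wider than they need be: in the first simulation, which reports them, standard errors did not fall when motor score was added, and the gain came through a conditional odds ratio further from 1. Second, the documents do not show that AIS grade and walking are the outcomes motor score predicts best. What counts is prediction beyond the covariates already in each model, and that is unknown.

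For walking, the firm finding is an ambiguity about the baseline covariate. If the model has baseline WISCI-II alone, adding motor score would cut the standard error by 0.5% to 20% for r from 0.1 to 0.6.

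**What to change.** Before the investigators are unblinded:

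1. **AIS grade.** Add baseline Total Motor Score as a fixed effect to the ordinal model, alongside baseline AIS grade, severity and site. State that the odds ratio is then also conditional on baseline motor score.
2. **WISCI-II.** State that the model includes both baseline WISCI-II and baseline motor score. This settles either reading of the present text.

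The cost is about one sentence for each outcome in the analysis plan and one more parameter per model. No new data are needed. The trade-off for AIS grade is the changed meaning of the odds ratio. If allocation-linked results have already been seen, the extended models should be reported only as labelled post hoc sensitivity analyses beside the planned ones.
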